### Data collection and management

#### Data collection overview

Physiological data will be collected continuously during the experimental sessions using a multimodal sensing setup. Questionnaire data will be collected at multiple timepoints. Table 1 summarizes all data that will be collected and their corresponding instruments.

**Table 1 tbl0001:** Data collection summary.

Instruments	Data collected	Data collection timing
Consumer-grade smartwatches	Sleep duration, sleep schedule	Participants screening, and throughout the experiment days
KSS questionnaire	Baseline and post-condition subjective sleepiness levels	Participants screening, pre-experiment session baseline, post-condition, end of wakefulness reset period
MCTQ questionnaire	Chronotype	Pre-experiment assessment
PSQI questionnaire	Subjective sleep quality over the past one month	Pre-experiment assessment
Big Five Personality	Personality traits	Pre-experiment assessment
Research-grade smart wristband	Blood volume pulse (BVP), heart rate variability (HRV), electrodermal activity (EDA), 3-axis acceleration, and skin temperature	Experimental sessions
Eye-tracking system	Pupil diameter of both eyes	Experimental sessions
Functional near-infrared spectroscopy (fNIRS) system	Changes in HbO_2_ and HHb in the prefrontal cortical regions, head movements captured by 3-axis acceleration	Experimental sessions
Video recorder	Used solely to identify observable yawning behavior (counts of yawning, eye closure duration); recordings will be permanently deleted after feature extraction	Experimental sessions
Simple Likert Scales	Stimulus naturalness and comfort ratings	Experimental sessions
Semi-structured interview	Post-experiment interview responses	Post-experimental assessment

#### Data storage and security

All data collected in this study will be handled in accordance with strict data protection and ethical guidelines. To protect participant privacy, data anonymization will be implemented at the time of enrollment. Each participant will be assigned a unique anonymous code, which will be used to label all data files. All physiological data files will be kept on a password-protected offline computer, while questionnaire data will be stored in encrypted digital formats. Video recordings will be stored only temporarily on a secure offline device for the sole purpose of behavioral feature extraction, such as identifying yawning occurrences and sleep onset timing. Once these behavioral codes have been extracted, all video recordings will be permanently deleted. Only the derived behavioral codes will be retained, and these will be incorporated into a fully de-identified dataset for analysis. Consistent file naming conventions (e.g., “ID_SessionNumber_Condition_DataType_Date”) will be used throughout the study to facilitate data processing, improve traceability, and reduce the likelihood of handling errors.

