#### Experimental procedure

Each experimental session includes two yawning stimulus conditions (with sound and without sound) presented in randomized, counterbalanced order. To minimize social presence effects on yawning responses [40,23], participants will remain alone in the experimental room throughout stimulus presentation, while the experimenter monitors the session remotely from an adjacent space via a live physiological data feed and video stream.

At the beginning of each condition, physiological recording will begin continuously, and participants will be instructed to watch the videos naturally and to maintain a comfortable and relaxed posture. No further instructions regarding yawning will be given at this stage, as participants will have been informed of their freedom to respond naturally at the pre-session assessment stage.

Stimulus presentation will then proceed for approximately 5 min. Each stimulus sequence will consist of approximately 50 discrete yawning events, each approximately 6 s in duration [41,42]. This duration is consistent with prior experimental yawning paradigms in contagious yawning research and falls within the commonly used 3–5 min exposure range [15,22]. During this period, all physiological signals will continue to be recorded continuously, and participant behavior will be monitored via the video recording. Particular attention will be given to signs of sleep onset such as sustained eye closure. If sleep onset occurs, the corresponding timestamp will be noted, and recording will continue without interruption.

Following stimulus presentation, a post-condition assessment period of approximately 10 min will be conducted. Video will be stopped, and subjective sleepiness will be assessed using the KSS. Participants will also complete a brief questionnaire regarding their yawning behavior, including whether they yawned or experienced an urge to yawn [40].

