#### Data pre-processing

Physiological and behavioral data will be time-aligned across sensing modalities using synchronized timestamps. For each yawning condition, physiological signals will be segmented into predefined analysis windows relative to stimulus onset.

Artifact removal will then be performed separately for each sensing modality. For wristband-based signals, visual inspection and accelerometer data will be used to identify motion artifacts, signal dropout, and periods of excessive movement, which will be excluded from further analysis. For eye-tracking data, periods of sustained eye closure indicative of potential sleep onset as well as poor-quality pupil measurements, will be excluded. For fNIRS data, standard preprocessing procedures including bandpass filtering and motion artifact correction will be applied, followed by the removal of segments affected by low signal quality. Raw optical signals will subsequently be converted into HbO_2_ and HHb concentration changes.

To ensure that analyses capture stimulus-related physiological responses rather than transitions into sleep, only data recorded prior to identified sleep onset will be included in confirmatory analyses. Data segments affected by excessive artifacts, signal loss, or sustained eye closure will be excluded from primary analyses. Baseline correction will be applied to all physiological measures to account for inter-individual differences in resting physiological states. Baseline values will be calculated for each participant using pre-stimulus periods and subtracted from condition-specific values or expressed as percentage changes, as appropriate.

Following signal cleaning, physiological features will be extracted for each experimental condition. BVP will be used to compute mean heart rate and HRV metrics, including SDNN, RMSSD, and frequency-domain measures. EDA data will be analyzed to derive tonic skin conductance level and phasic skin conductance responses. Pupil data will be used to calculate mean pupil diameter, pupil diameter variability and pupillary unrest index (PUI). Skin temperature data will be summarized using mean peripheral temperature and changes relative to baseline. For fNIRS data, temporal patterns of cortical oxygenation changes will be extracted. Finally, descriptive statistics will be used to summarize participant characteristics, baseline sleep measures, and data completeness.

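### The example file-naming convention would show the condition to those who code the video and inspect wristband signals, and no masking of them is stated

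*Protocol article*

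**What the plan says.** **File names.** The Data storage and security section gives the example template "ID_SessionNumber_Condition_DataType_Date". It says that consistent conventions of this kind "will be used throughout the study to facilitate data processing, improve traceability, and reduce the likelihood of handling errors".

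**Video.** The same section says that recordings are kept "for the sole purpose of behavioral feature extraction, such as identifying yawning occurrences and sleep onset timing". Once the codes exist, "all video recordings will be permanently deleted". Table 1 adds eye-closure duration and yawn counts to what is read from the video.

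**Live monitoring.** Under Experimental procedure, "the experimenter monitors the session remotely from an adjacent space via a live physiological data feed and video stream". The section also says: "If sleep onset occurs, the corresponding timestamp will be noted, and recording will continue without interruption".

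**Signal cleaning.** The Data pre-processing section states: "For wristband-based signals, visual inspection and accelerometer data will be used to identify motion artifacts, signal dropout, and periods of excessive movement". It keeps only data from before identified sleep onset for confirmatory analyses. It drops segments with excessive artefact, signal loss or sustained eye closure from primary analyses.

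**Blinding.** The only blinding described is in Yawning stimulus materials, where the two raters of candidate clips are unaware of the study hypotheses. It does not extend to those who code or clean participant data.

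**The concern.** Participants cannot be masked to the film they watch, but the people who score and clean their recordings can be. A template with a condition field works against this, because the label is read at the moment the file is opened for judgement.

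Two kinds of result are exposed. Yawn counts and sleep-onset times are outcomes in their own right, so a coder who expects more yawning in one condition can shift them directly. Sleep-onset, eye-closure and artefact calls act indirectly. They set how much of each physiological recording survives, so a call made sooner or more readily in one condition changes the data being compared. For the video-derived part, deletion removes the means of checking afterwards.

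**Working it through.** No sample-size, power or error-rate figure bears on this point, and the plan gives none to reproduce. The check sets the sections side by side.

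1. **Is the condition visible?** Under the example template, yes, if the *Condition* field holds a plain label. The other fields do not reveal it by themselves: session order and the order of sound conditions are randomised and counterbalanced (Overview), so the participant code, session number and date do not identify the film without the allocation list. The exposure comes from this one field.

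2. **Does judgement enter?** For wristband signals, yes: visual inspection is stated, alongside accelerometer data, with no threshold given. For video, the Ethics row of the Specifications table speaks of behavioural coding, and the article does not say whether a person or software does it. Limitations notes that there is no polysomnography to anchor sleep onset.

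3. **Do these calls decide which data are analysed?** Under Data pre-processing, sleep onset, sustained eye closure and artefact do. Yawn counts do not; Data analysis lists yawning as an exploratory outcome.

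4. **Which outcomes are reached?** The secondary physiological outcomes, through exclusion, and the exploratory yawning and sleep-onset outcomes, through coding. The primary outcome is the participant's own KSS rating. The exclusion rules concern recorded signals, and their stated purpose is to capture physiological responses to the stimulus.

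5. **Can the calls be checked later?** Video codes cannot, because only the derived codes are kept. Signal files can: Data storage and security deletes video only, so a masked analyst could repeat the artefact decisions. Eye-tracking data also record sustained closure, which gives a partial check on sleep onset.

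6. **Is there a second route?** Yes. Sleep onset is also timestamped during live monitoring. The article does not say that the person watching is unaware of the condition, and renaming files would not change that.

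**Size.** The article gives no rate of yawning, sleep onset, rejected segments or coder error, so no bias can be calculated. As an illustration only: if coders counted 10% too many yawns in one condition and 10% too few in the other, the rate ratio would be 1.1/0.9 = 1.22 with no true difference. The 10% is assumed, and with no error at all the ratio is 1. The illustration concerns an exploratory count and says nothing about the size of bias from excluded data.

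**The case against.** The strongest reply is that the template is only an example, that its condition field could hold a masked code, and that coder masking is the kind of detail a condensed article leaves to a fuller document. The first two parts are fair: a reader might infer that the plain condition stands in every file name, or that coding is declared unblinded, and the article says neither. The third does not dispose of the point. The concern rests on a convention that the article writes down and applies throughout, and following it as shown would disclose the condition. If a masked code is meant, one sentence would settle it.

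Other strong readings also go too far:

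- **That every exclusion is judged by eye.** Visual inspection is stated for wristband signals only. Eye-tracking exclusions rest on closure and measurement quality. fNIRS cleaning uses filtering, motion correction and signal quality. Table 2 bases the exploratory sleep-onset analysis on behavioural and physiological indicators together.
- **That nothing can be audited.** This holds for video codes, not for the retained signals.
- **That sound on the face video reveals the sound condition.** The article does not say that the camera records sound or how the stimulus audio is played.
- **That the authors lean heavily on these outcomes.** They promise caution in interpreting several exploratory outcomes, which limits the harm. It does not remove a bias that is cheap to prevent.

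**Conclusion.** The point holds in a limited form. Followed as illustrated, the naming convention would show the condition to those who code sleep onset, eye closure and yawns and to those who inspect wristband signals. No masking of them is stated. The secondary physiological and exploratory behavioural outcomes are open to condition-related coding bias as a result.

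A reader might infer that the primary result is at risk, since the exclusion rules mention primary and confirmatory analyses. The document does not support that: KSS is self-rated, and those rules are framed around physiological signals.

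The conclusion assumes that the field would hold a readable label and that a person makes at least some of the video judgements. Direction and size are unknown. It is worth correcting before coding starts, because the video-derived part cannot be repaired afterwards.

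**What to change.** - Replace the *Condition* field with a neutral random code. Make it unique to each recording, since a fixed letter per condition could be worked out. Hold the key apart from coders and signal cleaners.
- Code files in shuffled order, with any audio muted.
- Use the masked video code, not the experimenter's live timestamp, as the sleep-onset time for data inclusion. The live note can stay as a record.
- Lock the video codes before the videos are deleted. Deletion can still follow immediately after extraction, as the Ethics row of the Specifications table states, and need not wait for signal cleaning.
- Lock the artefact decisions before the key is opened.

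The cost is a renaming script and a key file, with no extra recordings or participants. Segmenting signals relative to stimulus onset needs the onset time, not the condition label, so processing is not held up. The small downside is that traceability, one of the stated aims of the convention, runs through the key until lock.

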#### Data pre-processing

Physiological and behavioral data will be time-aligned across sensing modalities using synchronized timestamps. For each yawning condition, physiological signals will be segmented into predefined analysis windows relative to stimulus onset.

Artifact removal will then be performed separately for each sensing modality. For wristband-based signals, visual inspection and accelerometer data will be used to identify motion artifacts, signal dropout, and periods of excessive movement, which will be excluded from further analysis. For eye-tracking data, periods of sustained eye closure indicative of potential sleep onset as well as poor-quality pupil measurements, will be excluded. For fNIRS data, standard preprocessing procedures including bandpass filtering and motion artifact correction will be applied, followed by the removal of segments affected by low signal quality. Raw optical signals will subsequently be converted into HbO_2_ and HHb concentration changes.

To ensure that analyses capture stimulus-related physiological responses rather than transitions into sleep, only data recorded prior to identified sleep onset will be included in confirmatory analyses. Data segments affected by excessive artifacts, signal loss, or sustained eye closure will be excluded from primary analyses. Baseline correction will be applied to all physiological measures to account for inter-individual differences in resting physiological states. Baseline values will be calculated for each participant using pre-stimulus periods and subtracted from condition-specific values or expressed as percentage changes, as appropriate.

Following signal cleaning, physiological features will be extracted for each experimental condition. BVP will be used to compute mean heart rate and HRV metrics, including SDNN, RMSSD, and frequency-domain measures. EDA data will be analyzed to derive tonic skin conductance level and phasic skin conductance responses. Pupil data will be used to calculate mean pupil diameter, pupil diameter variability and pupillary unrest index (PUI). Skin temperature data will be summarized using mean peripheral temperature and changes relative to baseline. For fNIRS data, temporal patterns of cortical oxygenation changes will be extracted. Finally, descriptive statistics will be used to summarize participant characteristics, baseline sleep measures, and data completeness.

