## Description of protocol

### Overview

This protocol employs a laboratory-based, randomized within-subject crossover experimental design to examine the associations between contagious yawning stimuli exposure and subjective and physiological indicators of sleepiness. The protocol follows a 2 × 2 factorial structure manipulating: (1) stimulus type (human vs. digital character yawning) and (2) auditory content (with vs. without sound), yielding four experimental conditions.

Participants complete two sessions on separate days. In one session, they view human yawning videos under both auditory conditions in randomized order. In the other session, they view yawning videos of digital characters under the same auditory conditions. The order of sessions (human first vs. digital first) will be counterbalanced across participants. The order of conditions will be randomized and counterbalanced to minimize systematic order effects.

A within-subject design was selected to maximize sensitivity to condition-related differences while controlling for interindividual variability in baseline sleepiness, circadian preference, and autonomic functioning. To mitigate potential fatigue or habituation effects, experimental sessions will be conducted on separate days with a minimum interval of one-day between sessions.

The protocol is designed to examine relative differences across yawning stimulus conditions and within-subject changes over time, rather than to isolate yawning-specific causal effects relative to neutral stimulus exposure. Accordingly, non-yawning control conditions are not included. This design enables focused comparison across stimulus modalities and representations while maintaining a manageable experimental duration within a multimodal physiological recording context, which is consistent with prior studies using contagious yawning stimuli [26,27]. Pre-stimulus baseline recordings will be obtained prior to each condition, which allows within-subject quantification of changes relative to a stable resting reference.

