### Phase 2: experimental sessions

The experimental phase consists of two intervention sessions conducted on separate days with a minimum one-day interval to minimize potential carryover effects related to fatigue or transient sleepiness. Each session corresponds to one stimulus type (human yawning vs. digital character yawning), with session order randomized across participants. Each session will follow an identical structure and last approximately 70 min. To minimize circadian confounding, experimental sessions will be scheduled at approximately the same time of day, typically between 14:00 and 16:00, consistent with prior findings that yawning exhibits circadian variation in both animals and humans [30,31]. The second session will be conducted within ±1–2 h of the first session whenever feasible. Sessions will be scheduled to avoid early morning or late evening when spontaneous yawning frequency is known to be naturally elevated [14,32,33].

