Finally, a video camera will be positioned to capture the participant’s facial expressions throughout the session. The camera angle will be adjusted to ensure a clear view of the face, and ambient lighting will be optimized to support subsequent behavioral coding. A brief test recording will be conducted to confirm that facial features are clearly visible.

To ensure consistency across participants, the experimental environment will be standardized. Room temperature will be maintained between 20 and 22 °C throughout the session. Lighting conditions will be controlled at a moderate and consistent level. External noise and potential interruptions will be minimized as much as possible. Participants will be seated comfortably in a chair with back support, and the display screen will be positioned at eye level and at an appropriate viewing distance to reduce physical strain.

Following equipment setup, a five-minute baseline physiological recording will be conducted. This duration was selected based on prior studies examining the signal lengths required to reliably derive downstream physiological and cognitive indices [[37], [38], [39]]. Participants will be instructed to sit quietly in a reclining chair and relax while maintaining their gaze on a neutral fixation point displayed on the screen. All physiological signals will be recorded continuously during this period. To avoid introducing confounding influences, no conversation or additional instructions will be provided during the baseline recording.

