Exploratory outcomes will include behavioral indicators of sleepiness, such as yawning occurrence and instances of sleep onset observed during the experiment. Additional exploratory analyses will examine the relationship between yawning behavior and both subjective and physiological outcomes. These relationships will be modeled using mixed-effect approaches where appropriate, which allows for the inclusion of both within-subjects (e.g., condition, time) and between-subjects (e.g., chronotype, baseline sleep quality) factors.

Statistical significance will be evaluated using two-sided tests with an alpha level of 0.05 unless otherwise specified. Results will be reported using effect sizes (e.g., estimated mean differences as quantified by Cohen’s *d* or Hedge’s *g*) alongside 95% confidence intervals and p-values. Given the exploratory nature of several outcomes, findings will be interpreted with appropriate caution, and emphasis will be placed on the direction, magnitude, and consistency of observed effects rather than statistical significance alone. The data analysis plan is summarized in Table 2.

**Table 2 tbl0002:** Data analysis plan.

Analysis Level	Procedure
Primary outcome analysis	▪ Analyze changes in KSS using linear mixed-effects models to account for the within-subject repeated-measures design ▪ Fixed effects will include stimulus type (human vs digital character yawning), auditory condition (with sound vs without sound), and their interaction. ▪ Subject will be included as a random effect with a random intercept to account for interindividual differences in baseline sleepiness. ▪ Where model convergence permits, random slopes for condition effects may be explored. ▪ Conduct planned comparison [50] to examine differences in subjective sleepiness between human and digital yawning stimuli, differences between auditory conditions (with vs without sound), and the interaction between stimulus type and auditory condition.
Secondary outcome analysis	▪ Apply the mixed-effects modeling framework used for primary outcome analysis to each physiological outcome, including HRV, EDA, skin temperature, pupil dynamics, and fNIRS measures. ▪ Analyses will focus on changes relative to baseline and associations with experimental conditions. ▪ Where appropriate, multiple comparison adjustments (e.g., Bonferroni or false discovery rate correction) will be reported as supplementary information.

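### The reason given for subtracting physiological baselines does not apply to the planned within-person contrasts, and the unsettled baseline level decides whether subtraction does nothing, helps or harms

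*Protocol article*

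**What the plan says.** On purpose, the Protocol article (Data pre-processing) says: "Baseline correction will be applied to all physiological measures to account for inter-individual differences in resting physiological states". On form, the same section says: "Baseline values will be calculated for each participant using pre-stimulus periods and subtracted from condition-specific values or expressed as percentage changes, as appropriate".

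On when the baseline is taken, three places differ:
- Overview: "Pre-stimulus baseline recordings will be obtained prior to each condition". That is four per person.
- Equipment and environment setup: "Following equipment setup, a five-minute baseline physiological recording will be conducted". This comes once in each session, so two per person.
- Data pre-processing: the wording can be read as one value per participant.

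On design, Phase 2 says: "Each session corresponds to one stimulus type (human yawning vs. digital character yawning), with session order randomized across participants". Human versus digital is therefore a comparison between two days within a person, while sound is compared within a day.

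On analysis, Table 2 carries the primary model over to every physiological outcome: fixed effects for stimulus type, sound and their interaction, plus a random intercept for subject. It adds: "Analyses will focus on changes relative to baseline and associations with experimental conditions".

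**The concern.** The stated purpose and the model do the same job twice. A participant's resting level enters all four of that participant's film values equally, so it cancels from each of the three contrasts, and the subject intercept absorbs what is left. Subtracting a baseline cannot improve those contrasts for the reason given.

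It can still change them for other reasons. A session or condition baseline also carries that day's or that moment's state, the sensor placement, and its own measurement error. Subtraction removes the first two and adds the third, with a slope fixed at 1. Whether this is a gain or a loss depends on which baseline is used and on variances that the article does not give. At stake is the precision of the secondary comparisons, above all human versus digital, which bears on the second research question.

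**Working it through.** The article gives no physiological SD, correlation or sample size, so there is no planned figure to reproduce. All variances, r and n below are assumptions, shown as ranges. The variances are sampling variances of the estimates, not the standard errors that a fitted model would print. Randomised order and no carryover are assumed.

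**One baseline per participant.** The same number is taken from all four values, so every contrast is unchanged with complete data. In one simulated data set of 24 participants the estimates for stimulus, sound and interaction were −0.031, −0.044 and −0.272 both before and after subtraction.

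**One baseline per session.** Both films of a session lose the same number, so sound and interaction do not move (−0.044 and −0.272 again). Only human versus digital changes (−0.031 became 0.299). Let the residual variance be 1 per film, vD the day variance and vb the baseline error variance. The variance of the human–digital contrast is:
- no baseline: 2(0.5 + vD)
- subtraction: 2(0.5 + vb)
- covariate with the within-person slope: 2(0.5 + vD − vD²/(vD + vb))

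With vb = 1:

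| vD | No baseline | Subtraction | Covariate | Subtraction ÷ covariate |
|---|---|---|---|---|
| 0.25 | 1.5 | 3.0 | 1.40 | 2.14 |
| 0.5 | 2.0 | 3.0 | 1.67 | 1.80 |
| 1 | 3.0 | 3.0 | 2.00 | 1.50 |
| 2 | 5.0 | 3.0 | 2.33 | 1.29 |

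Subtraction breaks even with no baseline at vD = vb, loses below that and gains above it. At vD = 2 and vb = 0.25 the ratio of subtraction to no baseline is (0.5 + 0.25)/(0.5 + 2) = 0.30.

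**One baseline per condition.** With equal variances and within-person correlation r, the variance relative to no baseline is 2(1−r) for subtraction and 1−r² for the covariate. The ratio of the two is 2(1−r)/(1−r²) = 2/(1+r).

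| r | Subtraction | Covariate | Ratio |
|---|---|---|---|
| 0 | 2.00 | 1.00 | 2.00 |
| 0.2 | 1.60 | 0.96 | 1.67 |
| 0.5 | 1.00 | 0.75 | 1.33 |
| 0.8 | 0.40 | 0.36 | 1.11 |
| 0.9 | 0.20 | 0.19 | 1.05 |

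Here all three contrasts are affected. Subtraction harms below r = 0.5 and helps above it.

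**Percentage change.** A person's contrast becomes 100 × (difference between films)/(that person's baseline). Even a single baseline per participant therefore rescales each person's contribution. In the same data set, with an assumed baseline level of 20, the sound estimate went from −0.044 to 0.130 percentage points. Both are small against their standard errors (0.278 and 1.381), but the correction is plainly not inert.

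**How the covariate must enter.** The planned random-intercept model was simulated with per-condition baselines (700 runs per setting, n = 12 and 24). With between-person SD three times the within-person SD and n = 24, a single baseline term gave 1.75 (sound) and 1.66 (stimulus) times the variance of no correction at r = 0. Its slope is pulled towards the between-person slope: it averaged 0.83 when the within-person slope was 0. Splitting the baseline into person mean and deviation gave 1.01 and 1.02. At n = 12 and r = 0 the split cost was 1.00 to 1.04.

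**The case against.** A reader might infer that subtraction is always either inert or a source of noise. The article does not support that. Human versus digital is a between-day contrast and the sensors are removed and refitted between sessions, so day and placement offsets are a real target. The table shows subtraction cutting the variance from 5.0 to 3.0 at vD = 2. At vD = 5 the three variances are 11, 3.0 and 2(0.5 + 5/6) = 2.67, and the covariate's advantage shrinks to 1.13. This stands.

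A reader might also infer that a covariate is better at no cost. A single unsplit term can be clearly worse than no correction, and even the split form has a slope to estimate. This stands too.

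Change from baseline is moreover a target in its own right. The Overview and Data analysis sections both say so, and with no neutral control the question of response to yawning rests on it. That is a good reason to keep change scores for within-session questions, but it does not rescue the reason given in Data pre-processing for the between-condition contrasts. Nor does it conflict with the covariate. Once participant mean and deviation are both in the model, value and simple change give identical contrasts, because they differ only by terms already fitted.

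For fNIRS the objection holds fully: the signals are defined as concentration changes, so the value itself is already relative.

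Finally, the choice between change score and covariate is often left to an analysis plan. That is fair for the choice itself. It is less so for a rationale that the article states and that does not fit its own model, and for a baseline level described in three ways.

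**Conclusion.** The point holds in a limited form. The stated purpose is redundant for the stimulus, sound and interaction contrasts. The actual effect of subtraction ranges from none, through a doubling or tripling of variance (r = 0 with per-condition baselines; vD = 0 and vb = 1 with a session baseline), to a large reduction. The baseline level and the unreported variances decide which.

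Apart from a few percent in very small samples, a split covariate is at least as precise as subtraction. The advantage is 2/(1+r) with per-condition baselines and about 2.1 to 1.3 for human versus digital with a session baseline over the range shown. These sizes rest on assumed equal variances and cannot be fixed from the article.

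It would be wrong to infer bias. With randomised order and no carryover, simple subtraction leaves the contrasts unbiased. The primary sleepiness analysis is not touched. Severity is low to moderate.

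**What to change.** 1. Reconcile Overview, Equipment and environment setup, and Data pre-processing on whether the baseline belongs to the session or to the condition. Replace the stated reason for correction.
2. In Table 2, for the between-condition contrasts of HRV, EDA, skin temperature and pupil measures, add that baseline to the mixed model as two covariates: the participant's mean baseline and the deviation from it. The outcome may be the value or the simple change. A session baseline will sharpen only human versus digital.
3. Keep change from baseline for within-session questions and for fNIRS.
4. Replace the open choice between subtraction and percentage change with a stated rule for each measure, noting that percentages rescale each person's contrast.

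The cost is a few sentences in Data pre-processing and Table 2, plus one slope to estimate per model. If the baseline is set at session level, no new recordings are needed. A per-condition baseline needs the recordings that the Overview already promises.
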